## Abstract

**Background:**

Acute exacerbation of chronic obstructive pulmonary disease (AECOPD) is the leading cause of mortality in chronic obstructive pulmonary disease (COPD). Traditional Chinese medicine (TCM) has been widely used in Asia as an adjunct treatment for AECOPD to improve the patients’ symptoms. Xuebijing (XBJ) injection is one of the major herbal medicines used in TCM. Previous small-sample clinical trials have proven its efficacy and safety in the treatment of AECOPD; however, the current data on XBJ as an adjunct therapy are insufficient. The present study will be a multi-center randomized clinical trial (RCT) to evaluate the efficacy and safety of XBJ injection in AECOPD and explore its influence on the immune function based on the altered levels of T cells.

**Methods:**

This study will be a prospective, randomized, placebo-controlled, blinded, multi-center trial. A total of 300 eligible patients will be randomly assigned to the treatment or placebo control group in a 1:1 ratio using a central randomization system. The treatment group will receive routine medication plus XBJ injection, and the control group will receive routine medication plus 0.9% NaCl injection. The patients will receive the corresponding treatment for 5 days starting within 24 h of enrollment. The primary outcome, the of rate endotracheal intubation, will be evaluated on day 28 after treatment. The secondary outcomes will include changes in immune and inflammatory indicators, respiratory support, mortality rate after 28 days, blood gas analysis, improvement in Acute physiology and chronic health evaluation (APACHE) II scores and clinical symptoms, and the length and cost of intensive care unit stay and hospitalization. The safety of the interventions will be assessed throughout the trial.

**Discussion:**

This is the first and largest randomized, controlled, blinded trial that evaluates the efficacy of XBJ injection as adjuvant therapy for AECOPD. The results of this trial will provide valuable clinical evidence for recommendations on the management of the disease and identify the underlying mechanisms.

**Trial registration:**

ClinicalTrials.gov, NCT02937974. Registered on 13 October 2016. Chinese clinical trial registry, ChiCTR-IPR-17011667. Registered on 15 June 2017.

**Electronic supplementary material:**

The online version of this article (10.1186/s13063-019-3204-z) contains supplementary material, which is available to authorized users.

## Background

Chronic obstructive pulmonary disease (COPD), common progressive inflammation of the lower airways, is characterized by persistent respiratory symptoms and restricted airflow [1]. COPD is currently ranked as the fourth leading cause of death in China; however, it is estimated to become the third leading cause of death worldwide by 2020 [1, 2]. A cross-sectional survey estimated that in China the overall incidence of COPD was 8.2% in residents > 40 years old [3]. A majority of the patients have relatively stable COPD (SCOPD); however, the average patient with SCOPD will experience two episodes of acute exacerbation of COPD (AECOPD) per year, thereby increasing mortality and morbidity [4, 5]. This condition has resulted in a growing economic and public health burden.

AECOPD is often induced by respiratory infection, with sustained worsening of the patient’s respiratory symptoms that results in additional therapy [6, 7]. It accelerates the decline of lung function, reduces health status, and contributes significantly to mortality [8–10]. Systemic inflammation and immune response are the major factors influencing the outcome and quality of life in patients with AECOPD [11]. Moreover, the dysfunction of immune regulatory mechanisms is essentially attributed to the progression of COPD [12]. Multiple immune cells, T helper (Th1, Th2, Th17) and regulatory T (Treg) cells are suggested to be critical in the regulation of the immune system in COPD [13, 14]. Especially, Treg cells exert immunosuppression effects due to the secretion of anti-inflammatory cytokines such as interleukin (IL)-10 and transforming growth factor beta (TGF-β). Recently, some studies demonstrated that patients with AECOPD had a significantly elevated percentage of CD^4+^Tregs as compared to patients with SCOPD and healthy controls [15, 16], which suggests immunosuppression in patients with AECOPD.

The Global Initiative for Chronic Obstructive Lung Disease (GOLD) 2016 [17] guideline for the management of AECOPD includes pharmacologic therapies (bronchodilators, corticosteroids, and antibiotics), adjunct therapies (diuretics and anticoagulants), and respiratory support (oxygen therapy and ventilation). Despite such treatment recommendations, acute exacerbation occurs frequently and is associated with a high rate of morbidity and mortality among patients with COPD [18]. Furthermore, adverse effects and patients’ tolerance of pharmacological and support therapies should be considered. Thus, further efficient and safe strategies are urgently needed for the management of exacerbation.

Traditional Chinese medicine (TCM) is extensively used in Asia as an adjunct to Western medicine in the management of AECOPD. Chinese herbal formulas combined with routine pharmacotherapy have shown promising benefits in relieving symptoms, reducing the incidence of COPD exacerbation, and improving the quality of life in patients with COPD [19–21]. Xuebijing (XBJ) injection is one of the major herbal medicines used in TCM. Since 2005, some small-sample clinical trials have evaluated the efficacy of XBJ injection as adjuvant therapy for AECOPD and reported that it could successfully inhibit inflammation, regulate immune function, and improve the patients’ symptoms [22–24]. Our previous study suggested that XBJ significantly improved survival in patients with severe pneumonia. Other studies [25, 26] found that XBJ markedly enhanced the apoptosis of CD^4+^CD^25+^ Treg cells and reduced the immunosuppressive activity. Therefore, the positive results implied that XBJ is a potentially promising herbal medicine for the treatment of AECOPD. Hitherto, sufficient data on XBJ as adjunct therapy in AECOPD are lacking, and the present clinical study is associated with the limitations of the methodology and sample size. Thus, we aimed to conduct a large-scale, multi-center, blinded randomized clinical trial (RCT) to evaluate the efficacy and safety of XBJ injection in AECOPD and explore the underlying mechanisms.

## Methods/design

### Study design and settings

The present study will be a randomized, placebo-controlled, blinded, multi-center trial to be conducted at nine medical centers (Table 1) in tertiary general Hospitals that were selected by the expert committee. A total of 300 patients fulfilling the eligibility criteria will be enrolled. Subsequently, the participants will be randomly divided into two groups (treatment (XBJ) group and control (placebo) group) in a ratio of 1:1. The protocol for this study has been developed based on the Standard Protocol Items: Recommendations for Interventional Trials (SPIRIT) checklist (Additional file 1). The study design is illustrated in Fig. 1.

**Table 1 Tab1:** Research settings

01	Department of respiratory medicine, Chinese People’s Liberation Army General Hospital
02	Department of emergency, Chinese People’s Liberation Army General Hospital
03	Department of respiratory medicine, First Affiliated Hospital of Chinese People’s Liberation Army General Hospital
04	Department of emergency, First Affiliated Hospital of Chinese People’s Liberation Army General Hospital
05	Chinese People’s Liberation Army General Hospital of Rocket Forces
06	Navy General Hospital of Chinese People’s Liberation Army
07	Beijing Shi Ji Tan Hospital, Capital Medical University
08	Tianjin First Center Hospital
09	The Fourth Affiliated Hospital of China Medical University

**Fig. 1 Fig1:**
[figure not shown]
Flow chart of the study design. APACHE, acute physiology and chronic health evaluation

### Objectives

The primary objectives of this trial are to (1) evaluate the efficacy and safety of XBJ injection in patients with AECOPD and (2) investigate the influence of XBJ on apoptosis and activity of regulatory T lymphocytes.

### Participants

#### Inclusion criteria

Patients fulfilling all the following inclusion criteria will be selected as study volunteers:Patients meeting the diagnostic criteria of AECOPD: post-bronchodilator forced expiratory volume in 1 s (FEV_1_)/forced vital capacity (FVC) < 0.70; exacerbation comprising respiratory symptomatic worsening and beyond normal day-to-day variations that lead to a change in medication; (GOLD 2016 [17]).Existing indications for potential admission: the symptoms significantly worsening; severe underlying COPD (respiratory muscle fatigue, paradoxical respiration, aggravated or new centralized cyanosis, peripheral edema, unstable hemodynamic and mental state deterioration); new physical signs; failure of initial medical management of acute exacerbation; presence of serious complications; frequent exacerbation; older age; and insufficient domestic support (GOLD 2016).Age between 40 and 85 years, male or female.Weight between 40 and 100 kg.Signed informed consent.

#### Exclusion criteria

Patients meeting any of the following criteria will be excluded from the trial.Pregnant and lactating women.Allergic to XBJ and its ingredients, or have severe allergies.Exacerbation observed for > 72 h.Mental illness with poor compliance.Severe primary disease (active pulmonary tuberculosis, asthma, cystic pulmonary fibrosis, pulmonary sarcoidosis, pulmonary interstitial fibrosis, unresectable tumors, blood diseases, Alzheimer’s disease, or HIV).Accompanied by pulmonary embolism, shock, diffuse intravascular coagulation (DIC), acute myocardial infarction, upper gastrointestinal bleeding, pneumothorax, cardiac function grade ≥ IV, severe liver and kidney dysfunction (sequential organ failure assessment (SOFA) score liver or kidney single ≥ 3 points).Combined with severe hypoxemia, patients with oxygenation index < 150 or invasive mechanical ventilation.Participation in other clinical trials in the previous 30 days.Patients who are unsuitable for participation or unable to participate in this trial according to the judgment of the investigators (hemodialysis for > 1 month after organ transplantation, existing risk of potential medical disputes, and heart failure limiting the amount of liquid intake).

### Recruitment, screening, and consent

The recruitment of the participants will take place in ten medical centers in tertiary general hospitals in north China. Each sub-center will post and distribute the printed recruitment posters inside and outside the hospitals. Patients with AECOPD who visit the sub-centers are invited to participate in the study. Patients who fulfill the inclusion criteria and provide signed informed consent will enter the screening period. The patients who meet the exclusion criteria are excluded from the study within 24 h. The recruitment duration will be 18 months from January 2017 to June 2018.

### Withdrawal or dropout criteria

Patients will not be included in the analysis if:The researchers find out after randomization that the participants were included by error or misdiagnosis.Participants were not administered the research medication as planned because:They received the research medication for > 24 h;They failed to receive the research medication;They received the research medication for < 5 days (not including the patients who were discharged due to improved health or death due to progression of the illness);The actual dosage was < 80% of the total dosage (compliance < 80%).The major data were missing, affecting the evaluation of the efficiency of the main indicators.Prohibited medication was used or the combined medication dosage exceeded that of the protocol, thereby affecting the evaluation of the efficiency.Due to complications or changes in the condition, other specific treatment measures were accepted that were not suitable for continuation in this study.Voluntary withdrawal.

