#### Precautions

The following precautions will be observed:The use of other injections simultaneously during the course of intravenous infusions is prohibited.Other injections should be separated into 50 mL 0.9% NaCl.Prohibited medicines include ulinastatin, and TCM injections, such as Tanreqing, Reduning, and Qingkailing with efficacy similar to that of XBJ.The routine treatment of AECOPD should be carried out simultaneously, and XBJ injection should not be used as a substitute.If medication is administered for < 5 consecutive days and the patients’ clinical symptoms improve significantly resulting in discharge or the condition deteriorates, necessitating other treatments, the administration of the research medication will be suspended. The data for the first day of withdrawal will be recorded to day 6, and the follow up will be continued until day 28.

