#### Routine medication for AECOPD

Routine medication for AECOPD will be administered follows:Both groups will receive routine medication according to the GOLD 2016 guideline, including oxygen therapy, antibiotics, bronchodilators, corticosteroids, fluid balance administration, nutritional support, thromboprophylactic measures, and ventilatory support.Indications for invasive mechanical ventilation: - patients meeting any of the following conditions can be provided invasive mechanical ventilation: inability to tolerate noninvasive mechanical ventilation (NIV); failure of NIV; respiratory or cardiac arrest; respiratory pauses with loss of consciousness or gasping for air; diminished consciousness; psychomotor agitation inadequately controlled by sedation; massive aspiration; persistent inability to remove respiratory secretions; heart rate < 50 bpm with loss of alertness; severe hemodynamic instability without response to fluids and vasoactive drugs; severe ventricular arrhythmias; or life-threatening hypoxemia in patients unable to tolerate NIV.Systemic glucocorticoid therapy may cause interference in the results of this study, and hence, the following regulations for the usage of hormones were proposed:Whether or not to use glucocorticoids is determined by the researchers according to the patients’ condition;If needed, a dose of 40 mg prednisone per day for 5 days is recommended according to the GOLD 2016 guideline; if the dosage or duration is exceeded, this is recorded;If the symptoms are exacerbated after glucocorticoid withdrawal, it can be used again;The cumulative dose and time of glucocorticoid use during the 28 days needs to be recorded.

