### Statistical analysis

An independent professional statistician and researcher will develop a complete statistical analysis plan for the trial, prior to the final analysis. The statistical analysis will be performed by the statistician in a blinded manner using the Statistical Analysis System (SAS) software version 9.2. The main analysis will be based on the full analysis set (FAS). According to the intention-to-treat principle, the FAS refers to a set of data on any participants who randomly receive at least one treatment. The per-protocol set (PPS), a subset of the FAS, includes data on only those participants who completed the trial without any violations of or deviations from the protocol. The FAS and PPS will be used for the assessment of efficacy. For the safety assessment, the safety set (SS) will be used, which includes patients who have received at least one safety evaluation after treatment.

All data, including the number of subjects included, drop-outs, elimination conditions, demographics, baseline characteristics, and efficacy and safety assessment, will be analyzed using different approaches. Descriptive and univariate statistics will be used to characterize the study participants and compare the baseline characteristics between the two groups. The primary outcome is the rate of endotracheal intubation, which will be determined by the Cochran-Mantel-Haenszel (CMH) test in the FAS population. We prefer to use the CMH chi-square test because it can deal with confounders of multi-center effects. Two-sided tests will be performed for all the other statistical analyses. The CMH chi-squared test or Fisher’s exact test will be used for comparing the categorical outcomes. The continuous outcomes will be analyzed by Student’s *t* test, while the AEs will be presented using descriptive statistics and compared using a chi-square test. A *P* value <0.05 will be considered to indicate statistical significance. Missing data will be explored and adjusted using the imputation method.

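### The withdrawal criteria exclude randomised patients from the analysis without limiting this to the per-protocol set, which conflicts with the intention-to-treat FAS and may lose some primary events

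*Protocol article*

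**What the plan says.** The section Withdrawal or dropout criteria opens with "Patients will not be included in the analysis if" and names no analysis set. Among the reasons listed are:

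- a short course, with improved discharge and fatal progression exempt: "They received the research medication for < 5 days (not including the patients who were discharged due to improved health or death due to progression";
- low compliance, with the limit given as a percentage: "The actual dosage was < 80% of the total dosage (compliance < 80";
- missing major data that affect evaluation of the main indicators;
- prohibited medication, or combined medication above the protocol's dosage, that affects the evaluation;
- a change in the patient's state: "Due to complications or changes in the condition, other specific treatment measures were accepted that were not suitable for continuation in this study";
- voluntary withdrawal.

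The Statistical analysis section says that the main analysis rests on the FAS and that the primary CMH test is done in the FAS. It defines that set as follows: "According to the intention-to-treat principle, the FAS refers to a set of data on any participants who randomly receive at least one treatment". It defines a PPS separately, as the subset without protocol violations or deviations, and says that missing data will be imputed.

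The Precautions section covers patients whose course is cut short by discharge on improvement or by worsening. If "the condition deteriorates, necessitating other treatments, the administration of the research medication will be suspended", and follow-up goes on to day 28. The Abstract sets evaluation of the primary outcome, endotracheal intubation, at day 28.

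**The concern.** Consider a patient who is randomised, treated for two days, worsens, stops the study drug and is alive. The Statistical analysis section puts this patient in the FAS. The Precautions section collects the day-28 outcome. The withdrawal section takes the patient out of the analysis. These three statements cannot all be followed.

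The conflict matters because the exclusion is tied to the outcome. The short-course rule exempts improved discharge and death from progression, but not a living patient who stopped because of deterioration, and that patient is plainly at risk of intubation. A rule of this kind can remove primary events after randomisation. Equal removal in both arms costs power. If XBJ changes who deteriorates or who stops early, removal differs between arms even under blinding, and the comparison is biased.

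**Working it through.** **1. The plan's own figure.** Inputs from the Sample size section: 15.2% control, 4.7% XBJ, two-sided α = 0.05, β = 0.2. With the pooled-variance formula and no continuity correction:

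n = [1.96·√(2·p̄(1−p̄)) + 0.842·√(p₁(1−p₁) + p₂(1−p₂))]² / (p₁−p₂)², with p̄ = (0.152 + 0.047)/2 = 0.0995.

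This gives 126.4, so 127 per group. Then 127/0.85 = 149.4, so 150. Both stated figures reproduce, and the sample-size arithmetic is not at issue.

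**2. Planned events.** 150 × 0.152 = 22.8 and 150 × 0.047 = 7.05, about 30 in total.

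**3. Method for the sensitivity check.** The document does not say what share f of intubated patients would meet a withdrawal criterion, so f is assumed. Removing them from numerator and denominator gives

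observed rate = p(1−f)/(1−pf), arm size = 150(1−pf).

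Power is the exact two-binomial probability that the pooled z test rejects in favour of XBJ, with arm sizes rounded. The planned CMH test by centre is approximated by this unstratified test.

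**4. Equal removal, planned effect true.**

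| f in both arms | Rates, control vs XBJ | Arm sizes | Events | Power |
|---|---|---|---|---|
| 0 | 15.2% vs 4.7% | 150, 150 | 22.8, 7.1 | 88.0% |
| 10% | 13.9% vs 4.2% | 148, 149 | 20.5, 6.3 | 85.2% |
| 25% | 11.9% vs 3.6% | 144, 148 | 17.1, 5.3 | 77.9% |
| 50% | 8.2% vs 2.4% | 139, 146 | 11.4, 3.5 | 61.2% |

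A normal approximation gives 86.3%, 82.8%, 76.1% and 59.6%, the same pattern slightly lower.

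The 15% attrition allowance does not protect against this. At f = 50% both arms still hold more than the required 127 patients, yet power is 61%, because the patients lost are the ones with events.

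**5. Unequal removal, no true effect (15.2% in both arms).**

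| Removed, control / XBJ | Apparent rates | Chance of a significant result favouring XBJ |
|---|---|---|
| 10% / 20% | 13.9% vs 12.5% | 5.3% |
| 25% / 50% | 11.9% vs 8.2% | 17.3% |

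The nominal value is 2.5%. With equal removal it stays at about 2.5%, so the inflation comes wholly from the imbalance.

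**6. What the text does not settle.** The compliance item carries no exemption, so read literally it could also remove a patient discharged early because of improvement. The direction of any bias is therefore not fixed by the wording.

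**The case against.** The strongest reply is that the list is an unlabelled definition of the PPS in a condensed article. Only the Statistical analysis section names a primary population, and most of the listed reasons are deviations of the kind that the PPS excludes. This is plausible, and it rules out saying that the plan declares two primary populations or has decided to discard events. It does not remove the defect, because the withdrawal section refers to the analysis without qualification and the two sections conflict until one is reworded. The conflict between excluding missing data and imputing them disappears once the list is confined to the PPS.

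Several stronger readings are tempting but not supported:

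- *All intubations would be deleted.* Intubation is not on the list. Ventilatory support and the indications for invasive ventilation appear under routine care. A patient intubated after completing 5 days does not meet the short-course rule, and death from progression is exempt from it. Only some events are exposed.
- *The item that begins "They received the research medication for" more than 24 h removes nearly everyone.* It sits under a heading for patients not given the medication as planned, so those who received the planned course fall outside it. It looks like a garbled line about the 24 h start.
- *The steroid rule contradicts the list.* The routine-medication section recommends a dose and adds "if the dosage or duration is exceeded, this is recorded". The list requires in addition that the excess affect the evaluation. The two are compatible.
- *An FAS that requires one treatment breaches intention to treat.* In a trial that blinds investigators and subjects, this is a common and modest restriction.

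It is also fair to say that 10% equal removal leaves power above the planned 80%, and that nothing in the document indicates that removal would differ by arm.

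**Conclusion.** The point holds as a contradiction in the wording that bears on the primary comparison. As written, a treated, living patient who stops before day 5 because of deterioration is in the FAS, is followed to day 28, and is barred from the analysis. If the withdrawal section were applied to the primary test, some intubations could be lost for reasons linked to the outcome.

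The size depends entirely on assumed removal fractions and can only be given as a range: power from 88% down to 85%, 78% or 61% for 10%, 25% or 50% equal removal, and a false-benefit chance of about 5% or 17% for the two unequal cases. These figures show sensitivity and do not forecast what the trial would lose. With about 30 planned events the design has little room for such losses, so the wording should be settled before the analysis.

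**What to change.** - Replace the opening of the withdrawal section with: *Patients will be excluded from the per-protocol set only if*.
- State in the Statistical analysis section that the primary FAS analysis keeps patients as randomised, and that intubation by day 28 counts regardless of drug stopping, compliance, concomitant medication or withdrawal from treatment (unless consent to use the data is withdrawn). Handle missing outcomes by the imputation already promised there. The requirement of at least one treatment may stay.
- Reconcile the item on more than 24 h of medication with the start within 24 h of enrolment and the 5-day course under Trial treatment methods.
- Reconcile the Emergency unblinding section, which withdraws unblinded cases and records their data only to day 6, with follow-up to day 28.

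No view is taken on when treatment should be stopped.

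The cost is mainly wording. Day-28 follow-up is already planned for patients who stop because of improvement or deterioration. Emergency-unblinded cases would need data beyond day 6 if the passages are reconciled in that direction. The statistical downside is slight dilution of the FAS estimate by non-compliers, and the PPS remains available alongside it.

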### Intervention

#### Trial treatment methods

After randomization, the participants will be categorized into two groups receiving either XBJ injection (specification, 10 mL/piece; packaging, 10 pieces/container) or placebo (0.9% NaCl injection, suggested specification, 200 mL). XBJ injection is provided and manufactured by Tianjin Chase Sun Pharmaceutical Co., Ltd., Tianjin, China (lot number Z20040033). The 0.9% NaCl injection is provided by each sub-center. Both groups will receive routine medication according to the GOLD 2016 guideline [17].

The treatment group will receive routine medication plus XBJ injection every 12 h (q12h) for 60 min; a total of 50 mL XBJ will be diluted to 150 mL using 100 mL of 0.9% NaCl injection. The control (placebo) group will receive routine medication plus 0.9% NaCl injection (dosage 150 mL, q12h for 60 min). The dosage and speed of injection for the placebo and XBJ injection groups (150 mL, q12h, intravenous drip for 60 min) will be identical. The patients will receive the research medication within 24 h of enrollment, and the treatment period is 5 days.

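### The withdrawal list excludes patients for more than 24 h of study drug, and it bars patients from the analysis without limiting this to the per-protocol set, against the FAS primary analysis

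*Protocol article*

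**What the plan says.** All references are to the protocol article.

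- **Withdrawal or dropout criteria** opens with "Patients will not be included in the analysis if" and lists the grounds. Under study drug not given as planned, the first is "They received the research medication for > 24 h". The others there are no drug received, fewer than 5 days of drug, and less than 80% of the total dose. The fewer-than-5-days item has one exemption: "not including the patients who were discharged due to improved health or death due to progression of the illness". Further grounds include missing major data, prohibited medication, voluntary withdrawal, and "Due to complications or changes in the condition, other specific treatment measures were accepted that were not suitable for continuation in this study".
- **Trial treatment methods** sets the regimen: "The patients will receive the research medication within 24 h of enrollment, and the treatment period is 5 days". The abstract agrees: "The patients will receive the corresponding treatment for 5 days starting within 24 h of enrollment".
- **Precautions** covers early stopping. If "the condition deteriorates, necessitating other treatments, the administration of the research medication will be suspended", and "the follow up will be continued until day 28".
- **Statistical analysis** bases the main analysis on the FAS, invokes the intention-to-treat principle, and defines the FAS by receipt of at least one treatment. The primary Cochran-Mantel-Haenszel (CMH) test is run in that set. The PPS is a subset of the FAS restricted to completers without violations or deviations. Missing data are to be imputed.

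**The concern.** The first defect is a criterion that cannot be meant. Anyone treated as planned receives drug for more than 24 h, so the item excludes the patients who followed the protocol.

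The second is a conflict over who is in the primary analysis. The lead-in speaks of the analysis without qualification, and the main analysis is the FAS. A patient dosed at least once who then stops early, falls below 80% compliance, takes a prohibited drug, is moved to other treatment or withdraws is out under one section and in under the other.

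Some of these grounds are related to the outcome. The exemption from the fewer-than-5-days item covers discharge for improvement and death, but not deterioration. A patient whose drug is suspended because the condition worsened is therefore removed, although Precautions follows that patient to day 28. Such patients are plausibly at the highest risk of intubation. Applied to the primary analysis, the list would discard events whose data have already been collected.

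**Working it through.** **1. The duration items side by side.** Let d be the time on study drug.

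| Time on drug | Ground for removal |
|---|---|
| d = 0 | drug not received |
| 0 < d < 5 days | fewer than 5 days, unless discharged improved or died |
| d > 24 h | more than 24 h |

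The three items cover every value of d. Read literally, the only patients left are those who stopped within 24 h through discharge for improvement or death. The only other 24 h limit on dosing in the article is the window from enrollment to first dose, so a late first dose is the natural meaning.

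**2. The two sections side by side.**

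| Patient, dosed at least once | Withdrawal list | FAS |
|---|---|---|
| Drug suspended for deterioration before day 5 | out | in |
| Less than 80% of total dose | out | in |
| Prohibited medication | out | in |
| Other treatment after a change in condition | out | in |
| Voluntary withdrawal | out | in |
| Major data missing | out | in, with imputation |

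Only the ground of no drug received agrees with the FAS definition.

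**3. The plan's sample size.** Inputs from Sample size: p1 = 0.152, p2 = 0.047, two-sided α = 0.05, β = 0.2. With p̄ = (0.152 + 0.047)/2 = 0.0995:

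n = [1.960·√(2p̄(1−p̄)) + 0.842·√(p1(1−p1) + p2(1−p2))]² / (p1−p2)² = (0.8297 + 0.3508)² / 0.105² = 126.4, so 127 per arm.

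127/0.85 = 149.4, so 150 per arm. Both stated figures reproduce. By the same normal approximation, power is 80.2% at 127 per arm and 86.3% at 150.

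**4. PPS-only reading.** The list removes no one from the FAS. The figures 127 and 150 stand, and power is 86.3% with all 150 per arm analysed.

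**5. Literal reading, illustrated.** Expected intubations are 150 × 0.152 = 22.8 and 150 × 0.047 = 7.05, in total 29.85. Assume that a fraction g of the intubated patients in each arm stopped drug before day 5 for deterioration and is removed. The article gives no value for g; the three below are assumptions. Then

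rate = p(1−g)/(1−pg), n = 150(1−pg).

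| g | Events removed | n, control / XBJ | Rates | Risk difference | Power |
|---|---|---|---|---|---|
| 0 | 0 | 150 / 150 | 15.2% v 4.7% | 10.5 points | 86.3% |
| 0.10 | 2.28 + 0.71 = 3.0 | 147.7 / 149.3 | 13.89% v 4.25% | 9.6 points | 82.8% |
| 0.25 | 5.70 + 1.76 = 7.5 | 144.3 / 148.2 | 11.85% v 3.57% | 8.3 points | 76.1% |
| 0.50 | 11.40 + 3.53 = 14.9 | 138.6 / 146.5 | 8.23% v 2.41% | 5.8 points | 59.6% |

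The 15% attrition allowance covers the loss of average-risk patients (127 of 150 remain, power 80.2%). It does not cover selective loss of events.

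**The case against.** The strongest reply is that Statistical analysis is the more specific section. It names the FAS as the primary population twice, and the listed grounds are typical deviations that fit its PPS definition. A full analysis plan and a blind review meeting are also announced. The item on more than 24 h would exclude almost everyone treated, so no analyst could apply it. This makes the PPS-only reading plausible, and it makes the first defect an editorial one. It does not remove the conflict: the list never mentions the PPS, the PPS definition never refers to the list, and the lead-in states a rule rather than leaving one open.

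The link to the outcome can also be questioned. Ventilatory support, with its indications for invasive ventilation, is listed under routine care, so intubation is not clearly one of the other treatment measures. Nothing says that study drug stops at intubation, and an intubation after a completed 5-day course is not caught by the fewer-than-5-days item. These points stand. They are the reason the removed fraction is unknown, and they argue for small rather than large values.

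Finally, removing the same fraction of events in both arms leaves the odds ratio unchanged, since the odds in each arm become p(1−g)/(1−p). The illustration therefore shows lost power and a smaller risk difference, not a distorted relative effect. At g = 0.10 power still exceeds the planned 80%. Both remarks are correct.

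**Conclusion.** The point holds as a contradiction in the text. The item on more than 24 h is wrong as written; that it means a late first dose is an inference, strongly supported by the dosing window. The unrestricted lead-in conflicts with the FAS definition and so with the population for the primary test.

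The consequence depends on the reading. Confined to the PPS, the list costs nothing in the primary analysis. Taken literally, its effect cannot be sized from the article. The power figures rest on assumed fractions of intubated patients removed, equal in both arms, and on the planned event rates. No difference between arms is claimed. The point should be fixed because it touches the primary population and some of the grounds are tied to deterioration. The stated sample size is not in question.

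**What to change.** Make two wording changes in Withdrawal or dropout criteria, before the blind review meeting:

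1. Limit the lead-in to the per-protocol set, so that the whole list defines exclusion from the PPS only.
2. Reword the item on more than 24 h as a first dose of research medication given more than 24 h after enrollment.

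Every randomized patient with at least one dose then stays in the FAS for the primary CMH test, using the day-28 follow-up that Precautions already provides. The cost is the edit itself: sample size, test and data collection do not change.
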